#### Intervention experiences, fidelity and acceptance

We use semi-structured interviews to capture participants’ *qualitative experiences* with the study and intervention. In addition, the app records the frequency, duration, pause or end of music listening as well as whether songs are skipped. We will use this quantitative information to assess the *quality of the playlists* as well as *intervention fidelity* (i.e., the extent to which the intervention was implemented as intended). All caregivers will use the System Usability Scale to rate *the user-friendliness of the app and tablet* (10 items; 1 = “do not agree at all” to 5 = “fully agree”; [47]) during the third home visit. Caregivers in the IG will additionally complete a self-developed paper-and-pencil questionnaire to assess their *overall experience* with the app, tablet, and intervention (14 items, e.g., “Would you want the person with dementia to continue with the listening sessions?”, 1 = “definitely not” to 4 = “definitely yes”).

### Statistical analysis

We will use SPSS (IBM Corp., Armonk, NY) and R (R Development Core Team, Vienna, Austria) to conduct all analyses. We will check whether there are meaningful differences between the baseline characteristics of the IG and CG. In accordance with the CONSORT statement both “intention-to-treat” and “per-protocol” (i.e., using the sample of participants who adequately adhered to the intervention protocol by completing at least five out of the 21 sessions) analyses will be conducted for comparison. We will also conduct sensitivity analyses to investigate whether missing data, baseline differences, or the total number of listening sessions has any impact on the outcomes.

For analysing the effect of the intervention on the primary outcome (i.e., individual goal attainment), caregivers’ GAS-ratings will be averaged for each participant across all specified goals. Then, we will use t-tests to compare the average goal attainment between members of the IG and CG. In the case of baseline differences in the IG and CG, we will conduct regression analyses to assess the impact of the intervention on individual goal attainment while statistically controlling for the relevant variables. In addition, we will calculate and compare the proportion of participants who completely or partially attained their goals, maintained the initial state, or reported mild/ severe deterioration of their goals in each group.

Secondary outcomes (including data from the daily assessments) will be analysed using multilevel models with two levels, with assessment points (level 1) nested in participants (level 2). Average treatment effects will be analysed by including group membership as a level-2 predictor (0 = CG, 1 = IG). Person-level moderator variables will be included only if necessary, in accordance with the results of the sensitivity analyses. For outcomes that will be assessed for people with dementia as well as for their caregivers (e.g., physiological stress), three-level multilevel models will be used to account for within and between dyadic effects. Assessment points (level 1) will be nested in participants (level 2), and participants will be nested within dyads (level 3). Full maximum likelihood estimation will be used to account for any missing data.

To analyse the data from the behavioural observations, we will compute frequency scores for time units 1–5 (i.e., 20 min of behavioural observation bevor IML; pre-intervention period in the IG), 6–10 (i.e., 20 min of IML in the IG) and 11–15 (i.e., 20 min of behavioural observation after IML; post-intervention period in the IG). These frequency scores will then be compared within and between both groups (IG vs. CG).

Finally, to assess feasibility and acceptance, we will use a qualitative content analysis to analyse the content of the semi-structured interviews. Video recordings are analysed qualitatively. We will also examine the descriptive statistics of the quantitative measures of playlist quality, intervention fidelity, user-friendliness of the app and tablet, and overall experience with the intervention.

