#### Randomization

Following the baseline assessment, a research assistant uninvolved in the assessments or implementation of the study will use a computer-generated randomization list from www.random.org to randomly assign participants by gender to either the intervention (IG) or control group (CG). A research assistant will contact the dyads by telephone to inform them about their allocation and schedule a first home visit. It will not be possible to blind participants to their treatment allocation due to the nature of the intervention.

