#### Primary outcome: individual goal attainment

Standardized outcome measures may underestimate the effects of IML. We therefore focus on participants’ *individual goal attainment* after six weeks of IML or treatment as usual as the primary outcome. We will use the Goal Attainment Scaling (GAS) approach to assess individual goal attainment [31]. The extent to which the individual goals formulated during the T0 telephone interview were attained will be quantified using a 5-point scale (-2 = “severe deterioration”; + 2 = “complete goal attainment”; [32]).

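### The primary t-test on mean goal attainment omits gender, the randomisation factor, and covariate adjustment depends on observed baseline differences, with no statement of which result is primary

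*Protocol article*

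**What the plan says.** All references are to the protocol article.

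- **Randomization.** A research assistant will "randomly assign participants by gender to either the intervention (IG) or control group (CG"). Read naturally, this is stratification by gender. The article does not use that word, does not say whose gender in the dyad is meant, and does not mention blocks.
- **Primary outcome.** Attainment of each goal "will be quantified using a 5-point scale" running from -2 to +2. Ratings are averaged over a participant's goals.
- **Statistical analysis, primary comparison.** "we will use t-tests to compare the average goal attainment between members of the IG and CG". No covariate is included.
- **Statistical analysis, next sentence.** "In the case of baseline differences in the IG and CG, we will conduct regression analyses", "while statistically controlling for the relevant variables". This stands in the primary-outcome paragraph and is not labelled supportive.
- **Statistical analysis, opening paragraph.** "We will check whether there are meaningful differences between the baseline characteristics of the IG and CG". The same paragraph announces "sensitivity analyses to investigate whether missing data, baseline differences, or the total number of listening sessions has any impact on the outcomes".

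Gender is not named in any model in that section.

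**The concern.** After a sound randomisation, observed baseline differences are chance. They are a poor guide to covariate choice: an imbalanced variable that does not predict GAS needs no adjustment, and a balanced variable that predicts it strongly is worth adjusting for. The stated rule uses imbalance alone. It also leaves out the one variable that the design itself singles out.

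Two things are at stake. First, when the trigger fires there are two estimates of the same effect and no statement of which answers the primary question. That matters more than usual here, because participants cannot be blinded and the GAS ratings come from the caregivers. Second, the T0 questionnaire already collects variables that could sharpen the comparison, and the rule uses them only by accident of imbalance.

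**Working it through.** **Inputs from the article.** f = 0.2, which is d = 0.4 for two equal groups; alpha 0.05, taken as two-sided; N = 98 dyads analysed (Sample size). Allocation is taken as 1:1. The article gives no variance explained by gender or by T0 variables, so those values are assumptions shown as ranges.

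**Starting point.** The exact noncentral-t power of a two-sided t-test with N = 98 and d = 0.4 is 0.500. The article states 0.95 for this N. That mismatch is a separate matter; N = 98 serves here only as a common base for comparison.

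**Step 1: effect of omitting gender.** Suppose gender is balanced across arms and explains a share R² of GAS variance. The t-test then keeps that share in its error term although it cannot contribute to the difference between arms. Under the null, approximately:

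rejection rate = P(|Z| > 1.96 / √(1 − R²))

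With equal numbers of each gender and a gender effect of δ within-gender SDs, R² = 0.25δ² / (1 + 0.25δ²).

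| δ (assumed) | R² | 1.96/√(1 − R²) | Type I error |
|---|---|---|---|
| 0.2 | 1.0% | 1.970 | 4.9% |
| 0.5 | 5.9% | 2.020 | 4.3% |
| 0.8 | 13.8% | 2.111 | 3.5% |

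Simulation agrees: 4.2-4.8% at δ = 0.5 (6,000 runs per scenario) and 3.45% at δ = 0.8 (20,000 runs). Adding gender alone at δ = 0.5 gives 5.0-5.5%, which is nominal within simulation error (standard error about √(0.05 × 0.95/6,000) = 0.3 points).

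**Step 2: how often chance fires the trigger.** The article sets no threshold. If a difference meant p < 0.05 on any of k independent baseline variables, the probability is 1 − 0.95^k:

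- k = 5: 23%
- k = 10: 40%
- k = 20: 64%

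**Step 3: operating characteristics of the rule.** Assumed settings: N = 98, 1:1 within gender; 5 or 10 baseline covariates with total R² of 0.1 or 0.3; gender effect 0 or 0.5 SD; each covariate adjusted for only if its baseline p < 0.05; 6,000 runs per scenario.

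| Analysis | Type I error | Power at d = 0.4 |
|---|---|---|
| Unadjusted t-test | see Step 1 for the effect of gender | 49-51% |
| Imbalance-triggered adjustment | 3.6-5.2% | 48-52% |
| Fixed adjustment, covariate R² = 0.1 | 4.6-5.5% (both R² values) | 49-54% |
| Fixed adjustment, covariate R² = 0.3 | as above | 61-68% |

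The t-test and the triggered regression disagreed on significance in 0.9-2.1% of null trials and 3-8% of trials at d = 0.4. Always taking the smaller p-value gave a type I error of 4.4-5.8%.

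**Step 4: analytic check on the power gain.** The effective effect size under adjustment is d/√(1 − R²):

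- R² = 0.1: 0.4/√0.9 = 0.422, power 54%
- R² = 0.2: 0.4/√0.8 = 0.447, power 59%
- R² = 0.3: 0.4/√0.7 = 0.478, power 65%

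The last figure lies inside the simulated 61-68%. At R² = 0.1 the simulated range reaches down to 49%, because ten weak covariates use up degrees of freedom.

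**The case against.** The strongest defence is that the article commits to the t-test without condition and only adds regression. Baseline differences are also listed among the sensitivity analyses, so the t-test can be read as primary and the regression as a check. An unadjusted t-test is valid in a randomised trial, the article is condensed, and covariate lists or thresholds may be in an analysis plan that is not shown.

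Much of this stands. A reader might infer that the regression replaces the t-test, so that the data choose the reported result. The text does not say so; it leaves the status of the two analyses open. The missing threshold and covariate list are not held against the article. What remains is a rule the article does state: adjustment for the primary outcome is conditional on observed imbalance. A later plan with fixed adjustment would have to depart from it.

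A reader might also extend the criticism to the secondary models, where "Person-level moderator variables will be included only if necessary, in accordance with the results of the sensitivity analyses". That sentence concerns moderators, and its trigger is the set of sensitivity analyses, which also cover missing data and number of sessions. It is not the same rule.

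Finally, the size depends on assumptions. The conservatism needs balance within gender, which the words on randomisation do not guarantee. The power gain is close to nil if T0 variables explain only 10% of GAS variance.

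**Conclusion.** The point holds as an unclear primary estimate and forgone precision. It does not hold as a false-positive problem, which a reader might infer from a data-dependent rule: followed mechanically, the rule has a type I error of 3.6-5.2%, and even picking the smaller p-value each time reaches only 5.8% in the scenarios examined. If gender is prognostic and balanced, the t-test errs on the conservative side, slightly for small gender effects and down to about 3.5% for an effect as large as 0.8 SD.

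The gain from fixed adjustment ranges from nothing to about 18 percentage points of power (from about 50% to at most 68%) as the variance explained by T0 covariates goes from 10% to 30%. The triggered rule captures almost none of it. All explained-variance figures are assumptions, and the trigger frequencies also assume independent variables and a 5% test. The change should be made because it is nearly free and settles which number is the trial's answer.

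**What to change.** In Statistical analysis, name one primary model: a linear regression of mean GAS on group, gender and a short fixed list of variables already collected at T0, for example the score for behavioural and psychological symptoms and the well-being rating. Use the same gender variable that the randomisation used, and fit the model whatever the observed balance. Report the unadjusted t-test as supportive. Delete the sentence that makes regression depend on baseline differences, and present baseline characteristics descriptively.

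No new data are needed. With gender and two T0 variables, residual degrees of freedom at N = 98 fall from 98 − 2 = 96 to 98 − 5 = 93. The covariate list should stay short, since many weak covariates can cancel the gain.

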### Sample size

Based on prior research on the effects of IML on people with dementia in the institutional care setting [18, 24, 27], we expect that IML will have small to medium effect sizes (f = 0.2) on our outcome variables. Given our two-group design, an α of 0.05, and a power (1 − β) of 0.95, a sample of *N* = 98 dyads will be needed in order to reliably detect effects. Drop out in studies with a similar target group has ranged from 18% [18] to 36% [28]. To account for drop out, we therefore aim to recruit *N* = 130 dyads.

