#### Well-being of person with dementia: self and caregiver perceptions

Based on the circumplex model of emotion [33], caregivers will use visual analogue scales ranging from 0 to 100 [34] to assess the person with dementia’s *emotional well-being* and *arousal* daily via the app and as part of the paper-and-pencil questionnaires assessments at T0, T1, T2, and T3.

To the extent possible, participants with dementia will provide self-reports of their well-being and quality of life. During each of the three home visits, participants with dementia will use the Dementia Mood Picture Test [35] to self-assess their *emotional well-being* by selecting which of six faces (bad mood, angry, sad, worried, good mood, happy) best represents their emotional state. Participants with dementia will also use the Heidelberg Instrument for the Quality of Life of Dementia Patients [36] to indicate their *overall life satisfaction* (1 = “not at all satisfied” to 4 = “very satisfied”).

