#### Dyadic interaction quality

Caregivers will assess the *dyadic interaction quality* daily via the app and as part of the paper-and-pencil questionnaire at T0, T1, T2, and T3. Caregivers will use a self-constructed questionnaire (8 items, e.g., “We experience moments of joy together”; 0 = “strongly disagree” to 4 = “strongly agree”).

After each home visit, a project member will answer a single item on the dyad’s *global relationship quality* (-2 = “very bad” to + 2 = “very good”). The project member will also complete a self-constructed *relationship quality questionnaire* (16 items; e.g., “They get along well with each other”; -2 = “completely disagree” to + 2 = “completely agree”, or “assessment not possible”).

Trained raters will additionally use videos of the home visits to assess the quality of the dyadic interaction. Three camera recordings are made: frontal view of the person with dementia, frontal view of the caregiver and recording of the overall setting.

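### The daily-assessment models do not prespecify the pre-randomisation T0 value as a covariate, which gives away precision on secondary outcomes

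*Protocol article*

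**What the plan says.** The App-based daily assessments section has caregivers rate five things each day, during the six-week intervention period only: their own well-being and arousal, the well-being and arousal of the person with dementia, and the interaction between the two.

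The same constructs are also in the paper questionnaires. Well-being and arousal of the person with dementia are rated "daily via the app and as part of the paper-and-pencil questionnaires assessments at T0, T1, T2, and T3", and interaction quality "daily via the app and as part of the paper-and-pencil questionnaire at T0, T1, T2, and T3". The Caregiver's well-being section gives the caregiver's own ratings the same schedule. Under Randomization, allocation follows the baseline assessment, so every T0 value precedes it.

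The Statistical analysis section puts secondary outcomes, explicitly including the daily data, into two-level models, or three-level models where both dyad members are rated. The average treatment effect comes from group as a level-2 predictor. On other person-level variables it says: "Person-level moderator variables will be included only if necessary, in accordance with the results of the sensitivity analyses". Those sensitivity analyses cover missing data, baseline differences and number of sessions, and no threshold is stated. No sentence enters an outcome's T0 value as a planned covariate.

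**The concern.** The daily series starts with the intervention, so it contains no baseline. Adding a time or group-by-time term would not supply one. Any adjustment for where a dyad started has to come from outside the series, and T0 is the clean source. T1 is a weaker choice because it falls after randomisation in an unblinded trial.

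Repeating a rating daily averages out day-to-day noise but not stable differences between people. Where those differences are large, they make up most of the error of the group coefficient, and a T0 rating of the same construct by the same caregiver can remove part of it. If T0 is left to a rule that depends on the data, that gain is mostly forgone, and the covariate choice stays open until the data have been seen.

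**Working it through.** **Inputs from the protocol article (Sample size).** The effect size: "we expect that IML will have small to medium effect sizes (f = 0.2) on our outcome variables". For two equal groups, d = 2f = 0.4. The planned size: "Given our two-group design, an α of 0.05, and a power (1 − β) of 0.95, a sample of *N* = 98 dyads will be needed".

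**Assumptions, not in the article.** Two-sided test; 1:1 allocation, so 49 per arm; f = 0.2 applied to the person's mean daily rating; correlation rho between the T0 rating and that mean, from 0.3 to 0.7.

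**1. The article's own figure.** A two-sample comparison with d = 0.4, two-sided 0.05 and 95% power needs 328 dyads (exact noncentral calculation), not 98. So 98 is not reproduced this way. That is a separate matter; here 98 serves only as the number analysed.

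**2. Power with group only.** Noncentrality = 0.4 × sqrt(49/2) = 1.980; critical t on 96 df = 1.985; power = 50.0%.

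**3. Power with T0 as covariate.** Residual SD = sqrt(1 − rho²), so effective d = 0.4 / sqrt(1 − rho²).

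| rho | effective d | power, 98 dyads | power, 130 dyads |
|---|---|---|---|
| 0 (group only) | 0.400 | 50.0% | 61.9% |
| 0.3 | 0.419 | 53.8% | 66.0% |
| 0.5 | 0.462 | 61.9% | 74.3% |
| 0.7 | 0.560 | 78.4% | 88.7% |

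The gain at 98 dyads is about 4, 12 and 28 points.

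**4. Which rho is plausible.** If T0 behaved like one more daily reading, rho with a mean of m days would be ICC / sqrt(ICC + (1 − ICC)/m). For m = 42 and an assumed between-person ICC of 0.3 or 0.7, this gives 0.53 or 0.83. T0 is a paper rating taken six weeks before the intervention, so the true value may be lower.

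**5. Chance imbalance.** The SD of the T0 difference between arms is sqrt(2/49) = 0.202 SD units. P(|difference| > 0.2 SD) = 2 × (1 − Φ(0.2/0.202)) = 0.32. Only rho times the imbalance reaches the unadjusted estimate. For an imbalance of 0.2 SD that is 0.3 × 0.2 = 0.06, 0.5 × 0.2 = 0.10 and 0.7 × 0.2 = 0.14 SD, or 15%, 25% and 35% of d = 0.4.

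**6. Does a conditional rule recover the loss?** Simulation with 49 per arm and 20,000 runs per setting, adjusting only if the T0 difference has p < 0.05 (an assumed trigger, since the article gives none):

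| rho | rule fires | power, conditional rule | power, always adjusting |
|---|---|---|---|
| 0.3 | about 5% | 51% | 54% |
| 0.5 | about 5% | 51% | 62% |
| 0.7 | about 5% | 51% | 78% |

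Under no effect, the unadjusted test rejects in 5.2%, 4.8% and 5.0% of all runs. Among runs with a T0 difference above 0.2 SD, it rejects in 7%, 9% and 12%.

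**The case against.** **The quoted sentence concerns moderators.** Strictly, a moderator changes the treatment effect; it is not a baseline covariate. A reader might infer that the plan uses group alone and shuts T0 out. The text says neither: it names group as a predictor and is silent on T0. What stands is that group is the only level-2 predictor named, nothing provides for T0, and the one rule on person-level variables is conditional on analyses that include baseline differences.

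**Covariate lists belong in the analysis plan.** That is often so, and the paragraph does not list time effects either. But the article goes further than silence: it sets a data-driven entry rule without a threshold. That choice can fairly be questioned here.

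**Baseline differences are already examined.** They are, in a group comparison and in sensitivity analyses. A reader might infer from the omission of T0 that the effect estimate is biased. It is not: over randomisations the estimate is unbiased and type I error holds. A reader might also equate a 0.2 SD imbalance with half the planned effect, but only rho times it carries through.

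**The calculation fits few of the outcomes.** This stands. Well-being and arousal are rated for both members, which makes four of the five daily outcomes candidates for the three-level models. There the base power differs, and the two-sample figures match only interaction quality directly.

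**The gain is assumed.** This also stands. The article gives neither rho nor ICC, and the time gap and the change from paper to app argue against assuming a high value. At rho = 0.3 the gain is only 4 points.

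**Conclusion.** The point holds as a matter of efficiency on secondary outcomes. Five daily outcomes have a pre-randomisation T0 value that the stated models do not prespecify, and a significance-type trigger would recover almost none of the lost power. For a single-person outcome at 98 dyads the loss is about 4 to 28 points of power over rho 0.3 to 0.7, with 12 points at 0.5 as an illustration rather than an estimate. It rests on d = 0.4 applying to the person mean and on the assumed rho. In about a third of trials of this size, T0 would differ by more than 0.2 SD; at 0.2 SD the unadjusted estimate moves by 15% to 35% of the planned effect.

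The analysis is not invalid, and the t-test on goal attainment is untouched. The change is worth making because the data are already being collected.

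**What to change.** In the Statistical analysis section, state that every multilevel model of a daily-assessment outcome, two-level or three-level, includes the T0 value of the same measure for the same target person as a fixed covariate, regardless of observed imbalance. Limit the conditional rule to other person-level variables.

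The cost is one sentence, one degree of freedom per model, and a stated simple way of handling a missing T0 value. No new data are needed.
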